### Procedure for unblinding if needed

Unblinding will be only permissible in the case that a participant suffers an adverse event and unblinding is necessary to provide them with appropriate care. These situations should be rare, as the community health workers providing the intervention are already not blinded and the participants themselves are not blinded (as the intervention does not allow for blinding of the participant or intervention delivery personnel).

## Data collection and management

### Plans for assessment and collection of outcomes

In the first stage of the primary intervention, fieldworkers will conduct a baseline survey of participant age, sex, educational/employment status, dwelling characteristics, household ownership of durable assets, and medical history (particularly noting pre-existing diagnoses of hypertension and cardiovascular disease). This is available as Supplementary Material 3. Typical daily dietary recall will also be collected to estimate daily baseline sodium intake. One-week and one-month dietary recall will also be collected to confirm the reliability of the 24-h recall (though emphasis will be placed on shorter recall timelines). Additionally, anthropometric measurements (i.e., body weight and height) of the participants will be recorded. Blood pressure will be measured by trained fieldworkers using Omron Series 3 automatic portable blood pressure cuffs (Omron Healthcare, Kyoto, Japan) while trial subjects are in the seated position in the left arm following 15 min of rest. Three measurements will be taken at least 5 min apart to ensure accurate capture, with the mean of the second and third measurements used in the final data analysis. Units of blood pressure will be recorded in millimeters of mercury.

Finally, in the end stage of the study, fieldworkers will conduct an endline survey of all participants to assess daily endline sodium intake (by daily dietary recall) and one-week dietary recall. Blood pressure will be measured again by the procedure described above.

### Plans to promote participant retention and complete follow-up

Given the nature of the study, aside from routine contact from the community health workers in the two intervention groups, no specific plans will be made to promote participant retention. Fieldworkers will perform a house visit to complete the follow-up to ensure minimum loss to follow-up. All primary and secondary outcome data will be collected for participants who discontinue or deviate from intervention protocols, given the analysis will be performed as intention-to-treat.

### Data management

#### Data quality assurance

Data quality will be ensured through multiple procedures of review and cross-checking.

#### Data quality assurance standards

Data collection performance will be checked every day by the supervisors while pretesting. Data collectors with low performance will be given an initial warning and will have to recollect the data and pre-test again. If a second incident occurs, the data collector will be terminated, and a different data collector will be assigned and trained to collect data.

#### Data security and management

Data security will be assured through different steps. At first, data will be directly sent to the server immediately following collection. In addition, as a contingency, all data collected in the server will be backed up to a drive. Daily backups will be kept on drive at the end of each day of data collection and be kept separate from the devices during collection. Furthermore, data collectors will send all collected data at the end of each day of data collection via server. Security details of the server will not be communicated to anyone outside the research team.

#### Roles and responsibilities of data collection supervisors

Data collection supervisors are responsible for checking data discrepancies on a daily basis and taking necessary actions. All filled questionnaires will be cross-checked by the data collection supervisors at the end of the day at field for internal validation. This will involve collecting data at the same time as the data collector and checking for discrepancies holding the supervisor’s data as standard. 20% of the data collected on any given day will undergo the agreement test. Data collectors will not be informed beforehand which household the test will be performed at. In case of any missing or inconsistent data, the respective households will be revisited by the field coordinator. Confidentiality will be maintained throughout the interview and analysis process, and de-identified data will be stored under password protection.

Data collected from the study will be housed physically at BRAC James P Grant School of Public Health (BRAC JPGSPH) in locked cabinets accessible only to the field research manager and the primary investigator. All study questions will be asked and responses collected using the SurveyCTO platform on handheld Android devices. Blood test reports for screening participants for renal disease will be obtained as physical printed report from the local clinical laboratory and manually entered into SurveyCTO. The physical reports will be destroyed at the end of the project duration. Aside from these and the signed consent forms, no other data will be captured on paper/physical media. At the conclusion of primary data collection, all data will be entered into an electronic SurveyCTO database with secure institutional Google Drive backup. The database will be password-protected, with the password known only to the two site primary investigators and the research manager. The BRAC JPGSPH site primary investigator and research manager will provide an electronic, de-identified, cleaned analysis dataset to the statistical team at the conclusion of the study. The SurveyCTO database will be kept active following the conclusion of the study for addressing long-term safety concerns of study participants.

### Confidentiality

No sensitive questions will be asked to the participants. The privacy and well-being of the participants will be prioritized if there are any unforeseen risks. Moreover, the interviews for enrollment and data collection will be conducted in a private setting to provide respondents with their rights to necessary privacy and breathing space.

Data collected from the study will be housed physically at BRAC JPGSPH in locked cabinets accessible only to the field research manager and the primary investigator. At the conclusion of primary data collection, all data will be entered into an electronic SurveyCTO database. The database will be password-protected, with the password known only to the two site primary investigators and the research manager. Aside from signed consent forms, no other data will be captured on paper/physical media. The BRAC JPGSPH site primary investigator and research manager will provide an electronic, de-identified, cleaned analysis dataset to the statistical team at the conclusion of the study. The SurveyCTO database will be kept active following the conclusion of the study for addressing the long-term safety concerns of study participants.

### Plans for collection, laboratory evaluation, and storage of biological specimens for genetic or molecular analysis in this trial/future use

Trained specialists will be recruited to collect blood specimens from adults residing in households of the salt-recipient participants. The samples will be stored by the hospital for the period of testing and destroyed once the reports are generated. Serum creatinine tests will be conducted on the collected blood samples.

Urine samples will be collected from children (under 18) residing in households of salt-recipient participants. Trained field workers will perform spot tests, and the samples will be destroyed once the results are recorded. These two tests will be conducted only once before the initiation of the intervention.

## Statistical methods

### Statistical methods for primary and secondary outcomes

Our primary outcome, systolic blood pressure (outcome 1), will be treated as a continuous variable. It will be analyzed using linear regression to estimate the magnitude of the treatment effect of each study arm intervention. The secondary outcomes of diastolic blood pressure (outcome 2), as well as SBP and DBP among hypertensive individuals (3 and 4), will similarly be treated as continuous variables, to be summarized using linear regression. The secondary outcomes of hypertension (2) and hypertension control (5) will be assessed as a binary variable, summarized as an odds ratio (OR) using logistic regression. Lastly, self-reported sodium intake (6) and low-sodium salt intake (7) will be treated as continuous variables and analyzed using linear regression.

In the primary analysis, we will regress the outcome onto a categorical variable for the study arm (control, or intervention arms 2 and 3). We will calculate three beta coefficients with corresponding p-values to estimate the magnitude of the treatment effect of each study arm (with units in millimeters of mercury). Namely, these three study/comparisons are (i) control vs. CHW education/information only; (ii) control vs. CHW education/information + direct LSSS provision; and (iii) CHW education/information only vs. CHW education/information + direct LSSS provision. The model will include baseline BP as a covariate for adjustment. Should there be variations in other baseline characteristics between groups, we will further adjust our model for residual potential confounding sources such as age, gender, and clinical comorbidities. Secondary analyses of continuous variables will be treated similarly. In the secondary analyses of binary variables, we will similarly regress the outcome over the categorical variable for the study arm and strata to yield odds ratios estimating likelihood of the outcome.

Prespecified subgroup analyses will include sex, age over 65 years, participants hypertensive at baseline, and individuals normotensive at baseline. We will test for significance in these subgroup analyses by the use of an interaction term between the study arm and the subgroup variable.

Standard errors will be adjusted for clustering using the robust sandwich estimator. *P*-values < 0.05 will be considered statistically significant for the purpose of hypothesis testing for the primary analysis. *P*-values < 0.05 will be considered statistically significant for secondary analyses of binary outcome variables. All primary and secondary analyses will be conducted “as randomized” (i.e., following the intention-to-treat principle).

### Interim analyses

We do not plan to take any interim measurements between enrolment and the endline survey. As such, no interim analyses or stopping guidelines are planned, as there is no endpoint to base a stopping rule upon. Furthermore, as our intervention is a dietary supplement available in the open market that does not require a physician’s prescription, we had no basis to suspect that there would be safety outcomes to obtain in interim analyses. This decision was supported by the fact that larger randomized clinical trials elsewhere in the LMIC setting testing a similar LSSS product failed to detect harm from the intervention [18, 19]. This is in the setting of our exclusion criteria being even more restrictive than these prior robust RCTs.

### Methods for additional analyses (e.g., subgroup analyses)

Subgroup analyses planned include assessing blood pressure improvement and hypertension control in participants who were identified as hypertensive at baseline during the initial survey. The same statistical tests noted above will be performed for this subgroup. As stratification will not be employed at randomization for these participants, all findings in this group will be considered hypothesis-generating and non-causal.

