**Enrolment:**									
**Eligibility screen**	60 days								
**Informed consent**	5 days								
***Baseline survey***	15 days								
**Allocation**		5 days							

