## Assignment of interventions: allocation

### Sequence generation

The allocation sequence will be generated using computer-generated random numbers. No stratification will be performed. To reduce the predictability of a random sequence, blocking will be performed via a separate document that is unavailable to the fieldworkers who enroll participants and/or assign interventions. The randomization allocation process will be performed by a separate team independent of the fieldworkers.

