### Implementation

The allocation sequence will be generated prior to study commencement by a study team member who will not be involved in the enrollment and assignment of participants to specific intervention arms. Fieldworkers trained in research methods and good clinical practice will enroll participants during a home visit. Afterwards, they will inform participants of the intervention arm they have been randomized to based on the assignment made by a non-fieldworker study team member (who will not be involved in the enrollment process).

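### Lack of stratification does not make findings in baseline-hypertensive participants non-causal, and the stated rule bars a causal reading of three of seven secondary outcomes

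*Protocol article*

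**What the plan says.** All references are to the protocol article.

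- *Methods for additional analyses* plans a subgroup analysis "assessing blood pressure improvement and hypertension control in participants who were identified as hypertensive at baseline during the initial survey", using the same tests as elsewhere. It then sets the interpretation: "As stratification will not be employed at randomization for these participants, all findings in this group will be considered hypothesis-generating and non-causal". No other reason is given.
- *Outcomes* lists seven secondary outcomes. Three are defined only in adults hypertensive at the baseline survey: SBP, DBP and hypertension control. Hypertension means SBP of at least 140, DBP of at least 90, or self-reported antihypertensive treatment.
- *Sequence generation* states "The allocation sequence will be generated using computer-generated random numbers" and, for every factor, "No stratification will be performed".
- *Statistical methods for primary and secondary outcomes* analyses the three outcomes by arm with linear or logistic regression. It also names four subgroups (sex, age over 65, hypertensive and normotensive at baseline) and says of them: "We will test for significance in these subgroup analyses by the use of an interaction term between the study arm and the subgroup variable". The same section adds: "All primary and secondary analyses will be conducted “as randomized” (i.e., following the intention-to-treat principle".
- The timeline table places the baseline survey under enrolment, ahead of allocation, although an assessment row also marks it at time 0. *Implementation* has fieldworkers enrol participants first: "Afterwards, they will inform participants of the intervention arm they have been randomized to".

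**The concern.** The plan treats stratified randomisation as a condition for causal inference within a subgroup, and it is not one. A subgroup defined by a characteristic fixed before allocation inherits the randomisation of the whole trial.

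What is at stake is the conclusion the trial may draw. Under this sentence, a clear difference between arms in baseline hypertensives could not be reported as an effect of the intervention, although the design supports that reading. The sentence also gives readers the wrong reason for caution. The sound reasons, limited precision and several tests, are not mentioned.

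**Working it through.** The plan attaches no figure to this statement, so there is none to reproduce. The check has three parts.

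**1. The logic.** Let A be the arm, S = 1 mean hypertensive before allocation, and Y(a) be the outcome under arm a. Randomising households makes A independent of S and of all Y(a). Then

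E[Y | A = a, S = 1] = E[Y(a) | A = a, S = 1] = E[Y(a) | S = 1],

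and the difference between arms within S = 1 is the mean causal effect in that group. No step uses stratification. The two conditions that matter are that S is fixed before the arm can influence it and that everyone is analysed in the randomised arm. Stratifying on S would only make the number of hypertensives per arm more even.

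**2. Consistency within the plan.** *Sequence generation* excludes stratification for any factor. If missing stratification made a subgroup non-causal, the sex and age-over-65 subgroups would be non-causal too. The plan labels only the hypertensive group that way.

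**3. Simulation of the design.**

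Inputs from the protocol: 206 participants per arm, taken as 103 households of two adults (309 households in all); SD 20 mm Hg; ICC 0.25; effect 2 mm Hg; adjustment for baseline BP; cluster-robust standard errors.

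Assumptions not in the protocol: hypertension prevalence 20%, 30% or 40%; hypertension defined by SBP alone; baseline-endline correlation 0.6. A true effect of 5 mm Hg was added for comparison.

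Expected hypertensives per arm are prevalence × 206: 0.20 × 206 = 41.2, 0.30 × 206 = 61.8 and 0.40 × 206 = 82.4.

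Each scenario had 4000 replicates with unstratified household randomisation. The analysis was restricted to baseline hypertensives and compared LSSS with control at a nominal two-sided 5% level.

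| Prevalence | True effect (mm Hg) | Mean estimate | Monte Carlo SE | SD of estimate | Rejection rate |
|---|---|---|---|---|---|
| 20% | 0 | +0.05 | 0.06 | 3.72 | 6.0% |
| 20% | −2 | −2.11 | 0.06 | 3.67 | 9.1% |
| 20% | −5 | −5.14 | 0.06 | 3.61 | 29.6% |
| 30% | 0 | 0.00 | 0.05 | 3.03 | 5.7% |
| 30% | −2 | −1.89 | 0.05 | 3.02 | 10.3% |
| 30% | −5 | −5.02 | 0.05 | 3.07 | 38.9% |
| 40% | 0 | +0.02 | 0.04 | 2.59 | 4.9% |
| 40% | −2 | −2.04 | 0.04 | 2.63 | 12.0% |
| 40% | −5 | −4.97 | 0.04 | 2.62 | 48.0% |

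The largest departure from the true effect is 5.14 − 5 = 0.14 mm Hg. Departures go in both directions and are small beside the SD of a single estimate. Rejection under no effect is about 5 to 6%. Validity is therefore kept without stratification, and the weakness is precision. The simulation has no exclusion of households after randomisation, so it does not speak to that threat.

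**The case against.** The strongest defence is that the sentence errs on the safe side. It restrains claims, cannot produce a false positive and alters no estimate, model or sample size. With power of roughly 9 to 12% for 2 mm Hg under the assumptions above, *hypothesis-generating* is a suitable label. All of this stands, and it confines the point to the word *non-causal* and the reason given for it.

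A reader might also infer that the plan contradicts itself, by giving these three outcomes an interaction test in one section and denying them causal meaning in another. The document does not support that. The three outcomes get regression by arm. The interaction test belongs to the subgroup variables in the full sample, and an outcome defined only in hypertensives cannot carry an arm-by-hypertension interaction. Nor does listing an outcome as secondary conflict with reading its results as hypothesis-generating.

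A further objection is that simply declaring these to be randomised comparisons could overclaim, and this stands. *Recruitment* randomises 362 households and then plans to exclude those with CKD or nephrotic syndrome. The section on biological specimens confines testing to households of salt recipients. *Eligibility criteria* instead keeps such households in their arm under intention to treat. If the exclusion were carried into the analysis, it could act differently by arm. That threat would apply to every outcome, and it is not the reason the plan gives.

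**Conclusion.** The concern holds in a limited form. Lack of stratification does not justify *non-causal*, and the rule takes a causal reading away from three of seven secondary outcomes. No estimate or test changes, and the primary outcome is untouched.

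The causal reading rests on two conditions. Hypertension status must be settled before allocation, which the timeline largely supports, although it also marks the survey at time 0. All randomised households must be analysed as randomised, which *Eligibility criteria* and *Statistical methods* say but *Recruitment* leaves in doubt.

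The precision figures depend on the assumed prevalence and correlation. The argument about stratification does not depend on them.

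**What to change.** In *Methods for additional analyses*, delete *non-causal* and the clause about stratification. Replacement wording could be: *Comparisons between arms within participants hypertensive at baseline are randomised comparisons, with all randomised households analysed in their allocated arm. Hypertension status is taken from baseline survey data collected before allocation, using the definition under Outcomes, including reported antihypertensive medication. These results are regarded as exploratory because of limited precision and multiple testing.* The last sentence is needed only if the exploratory status is kept.

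Keep the full definition of hypertension. Classifying by the blood pressure reading alone would drop participants who are treated and controlled, and would change the population of all three outcomes.

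The exclusion described in *Recruitment* must be reconciled with the intention-to-treat statements in *Eligibility criteria* and *Statistical methods*, so that it is clear which households enter the analysis.

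The change to the subgroup section is wording only, with no new data, model or sample size. Reconciling the exclusion is a separate clarification that every outcome needs.

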### Methods in analysis to handle protocol non-adherence and any statistical methods to handle missing data

Analyses will be performed on an intention-to-treat basis. If missing data is < 5%, complete case analysis will be utilized. For missingness greater than that, multiple imputation will be utilized by chained equations.

### Plans to give access to the full protocol, participant-level data, and statistical code

Deidentified datasets analyzed during the current study and statistical code are available from the corresponding author on reasonable request, as is the full protocol. Public access will not be granted to the full participant-level dataset, but the full protocol and statistical code will be available to the public upon request to the investigators. Following the publication of the primary analysis, a de-identified version of the dataset, along with the statistical code will be publicly available via the Stanford Digital Repository.

## Oversight and monitoring

### Composition of the coordinating center and trial steering committee

The coordinating center will be based at the BRAC James P Grant School of Public Health, BRAC University (BRAC JPGSPH). As previously noted above, BRAC JPGSPH has already worked with the target population community, with many of the potential study participants previously enrolled into research studies by the institution as part of a larger Wellcome-trust funded multinational biobank to better understand the patterns and determinants of cardiovascular health in South Asian people in a cross-sectional analysis. BRAC JPGSPH also has substantial experience working with and evaluating interventions using community health workers. The BRAC JPGSPH team involves multiple investigators with extensive experience in epidemiology, noncommunicable disease research, community health research, and clinical trials in this setting. As such, the BRAC JPSGSPH coordinating center team’s role will be as equal collaborators on the study design and primary team for the on-the-ground subject recruitment, personnel management, and trial protocol enactment. This coordinating center will also be the principal team for liaising with and disseminating the results of the study to local and national stakeholders.

These members will supervise the day-to-day operations of the present study, including:Drafting, revision, and defense of study protocols and Bangladesh-level human subjects research ethical approval protocols;Recruitment, training, equipment, and evaluation of study fieldworkers;Recruitment, training, equipment, and evaluation of study intervention community health workers;Identification, testing, and purchase of intervention LSSS product;Recruitment of study subjects;Randomization of study subjects (including generation and implementation of the randomization allocation sequence);Primary data collection, security, and integrity confirmation. This process will involve data de-identification and management as well.

BRAC JPGSPH study team members will also be involved in the entire data analysis and publication/results dissemination phase and will be primarily responsible for the dissemination of results within Bangladesh and with national stakeholders (e.g., the Ministry of Health).

The Stanford University School of Medicine team also has substantial experience in epidemiology, chronic disease research, and clinical trials in the global health arena. The role of this center will be to provide logistical guidance on protocol design and primary statistical analysis of the resultant data. The members of the team will be responsible for:Drafting, revision, and defense of study protocols and obtaining human subjects research ethical approval protocols at Stanford;Assistance with drafting and revising documentation used for the recruitment, training, equipment, and evaluation of study fieldworkers;Assistance with drafting and revising documentation used for recruitment, training, equipment, and evaluation of study intervention community health workers;Performing primary data analysis on the de-identified final dataset;Drafting of abstracts and publications resulting from the findings of the primary data analysis;The Stanford-based team will be responsible for dissemination of results within Stanford and local stakeholders (e.g., the King Center on Global Development).

Meetings within each center will happen on a regular basis (weekly to monthly) with ad hoc meetings as unexpected issues may arise. Teams from both institutions will meet in full at the start and close of the trial, as well as following primary data analysis. Otherwise, individuals from each team will meet as necessary virtually throughout the duration of the study, from inception/planning through publication/dissemination of results. No specific steering committee will be appointed, to allow for rapid vertical transmission of information as needed and for all members of the study team to voice concerns or opportunities for improvement of the trial freely at any time.

